#### Visit 8 (week 56)

4.1.5

At this end-of-treatment visit:

- Safety will be reviewed, as above.- Neuropsychological and cognitive deterioration tests will be completed again.- Urine samples will be collected, and a blood test will be performed.- A dietary survey to assess patient adherence to the low phytate diet will be completed.- Any surplus supplement capsules will be collected, counted, and accounted for.- The doctor will perform a complete physical examination, including taking height and weight measurements, to check the patient’s general state of health.- Vital signs will be measured, including heart rate, blood pressure, and body temperature.- A non-contrast MRI and ophthalmological tests will be performed this week.- Body composition assessment will be carried out using vectorial BIA and Nutritional Ultrasound to measure the diameter of the rectus femoris of the quadriceps and preperitoneal visceral adipose tissue (51).- Pittsburg Sleep Quality Index will be administered.

#### Visit 9 (week 62)

4.1.6

In the follow-up visit:

- Questions about health and disease will be carried out.- Their vital signs will be measured, including heart rate, blood pressure, and body temperature.- Complete physical examination will be performed.- A routine blood test will be carried out.

### Manufacture of phytate and placebo

4.2

The phytate supplement and the placebo were purchased from the company Devicare S.L. The phytate will be administered in the same pharmaceutical form as the Lit-Control^®^ pH Balance dietary supplement with national code (CN) 183677.9. The placebo treatment will be manufactured at ELABORADOS DIETÉTICOS S.AU., as a sub-contracted manufacturing plant with Good Manufacturing Practice certification.

## Results

5

### The main variables (according to the main objectives) will be the following:

5.1

Progression of cognitive impairment as a dichotomous variable defined as a score decrease >1 SD in MoCA or in any of the cognitive domains studied [visual scanning and processing speed (DSST, TMT-A), divided attention and executive function (TMT-B and verbal fluency), learning, retention memory and verbal recall (RAVLT), praxia, visual memory (ROCF) and language (BNT)] at week 0 and week 56.Differences in the quantification of the iron deposit assessed by nuclear magnetic resonance (NMR) (T2W (R2* and R’2; QSM) (General Electrics, Signa Explorer 1.5T) at week 0 and week 56. We quantify iron content in specific brain areas using magnetic resonance imaging (MRI) techniques such as quantitative susceptibility mapping (QSM) or R2* relaxometry (53). QSM describes the magnetizability of a material to an applied magnetic field and is a substance-specific value (54). Iron causes MRI images to darken at a rate proportional to the iron load, with the half-life of this darkening defined as T2* (55). The rate of darkening, designated as R2*, is the reciprocal of T2* and is proportional to the iron content of the tissues (55). MRI scanning estimates tissue iron concentration both by gradient echo imaging, which provides T2*, and spin echo imaging, which provides T2, the reciprocal of R2 (55). Novel NMR techniques allowed an improvement of tissue metal mapping methods and also the understanding of the ferroptosis mechanisms (53, 55).

### The secondary variables (depending on the secondary objectives) will be the following:

5.2

Quantitative differences detected by the different cognitive tests (W0 and W56).Morphological differences in the MRI without contrast (W0 and W56): degree of atrophy of the medial temporal lobe (Scheltens score) (56), periventricular intensity and hyperintense lesions in deep white matter (Fazekas scale) (57), and number of lacunar infarcts detected.Differences in retinal neurodegeneration parameters and evolution of diabetic retinopathy (W0 and W56).Retinal function: best-corrected visual acuity (BCVA) and macular perimetry.Structural evaluation of the retina:Seven-field retinography and staging of diabetic retinopathy according to the Early Treatment Diabetic Retinopathy Study (58). Image of the disk-centered fundus, used to study the caliber and morphology of the vessels.Wide-field images with and without fluorescein to examine the peripheral retina and the degree of hypoperfusion (59) ^(^
60
^),^.Optical coherence tomography (OCT-SD) to assess neurodegeneration and macular edema parameters such as retinal nerve fiber layer (RNFL) thickness, ganglion cell layer (GCL) thickness, and choroidal thickness will be collected (61).OCT-angiography: to evaluate in detail the capillary plexuses of the macula, both the vessel density (VD), perfusion density (PD) in both superficial capillary plexus, and the foveal avascular zone (FAZ) will be collected (60).Effect on AD biomarkers (W0 and W56):Inflammation mediators: TNF-a, IL-1b, and IL-6 (Multiplex)Neuronal injury markers: neurofilament (NF) (SimoaTM)AD biomarkers: t-tau, p-tau181, Ab42 and Ab40 (ELISA)AGEs and RAGEs (ELISA)Differences in sleep quality reported by Pittsburg Sleep Quality Index.Differences body composition assessed with vectorial bio-impedance analysis and Nutritional Ultrasound to measure the diameter of the rectus femoris of the quadriceps and preperitoneal visceral adipose tissue.Effect on hand grip strength dynamometry in the dominant and contralateral hand.

### Other variables

5.3

Other variables include the following:

As the cognitive status of participants can be influenced by depression and educational level, this information will be collected, and a Beck Depression Inventory test will be performed to assess depressive symptoms (W0 and W56).Laboratory parameters (W0, W14, W28, W42, W56, and W62). Glucose, HbA1c, liver profile, iron, ferritin, transferrin, transferrin saturation, calcium, phosphate, 25-(OH)-vitamin D (W0, W28, W56, and W62), PTH (W0, W28, and W56), creatinine, profile lipid, complete blood count, microalbuminuria/creatinine (W0, W28, and W56), and cystatin C, insulin, and hsPCR (W0 and W56). FIB-4 will be calculated.Urinary phytate in 2 h urine (W-4, W28, and W56) (62).Clinical history and results of physical examination: age, sex, race, educational level, date of diagnosis of T2DM, height (W-8, W0, and W56), weight, BMI, blood pressure, heart rate, waist circumference (W0, W14, W28, W42, W56, and W62), hypertension, cardiovascular disease, diabetic retinopathy, alcohol and tobacco consumption, history of polyneuropathy (W-8, W0, and W56), treatment of T2DM, and intake of other medications (W0, W14, W28, W42, W56, and W62).

### Statistical analysis

5.4

For the analysis of primary and secondary objectives, differences within groups will be assessed using ANOVA for repeated measures, and difference between groups will be assessed using ANCOVA for repeated measures. Qualitative variables will be analyzed using the chi-square test or the McNemar’s test. The analysis will be adjusted for confounding variables. With regard gender dimension, women have a higher risk of dementia; therefore, an additional analysis will be carried out, stratifying results by sex. A value of p<0.05 will be considered an indicator of a significant difference. The analysis will be performed using SPSS software (IBM Corp., version 24.0).

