### Description of interventions

4.1

Patients will have nine visits between week −8 (−8) and week 56 (w56), with week 0 (w0) being the point of randomization and start of treatment. These visits will take place in the endocrinology service of the Son Llàtzer University Hospital. **Figure 1** sums up the different interventions that will take place in each visit. Furthermore, a follow-up visit will be performed at week 62 (w62).

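### Section 5.4 names a repeated-measures ANCOVA for the between-group comparison but not the tested term or the week-0 covariate; for outcomes measured only at weeks 0 and 56, one literal reading estimates half the treatment effect

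*Protocol article*

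**What the plan says.** Section 5.4 (Statistical analysis) gives one rule for the primary and secondary objectives. Within arms, "differences within groups will be assessed using ANOVA for repeated measures"; between arms, "difference between groups will be assessed using ANCOVA for repeated measures". On covariates it adds only: "The analysis will be adjusted for confounding variables". The software is SPSS. Categorical variables go to chi-square or McNemar tests.

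The outcomes concerned have two measurements:

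- Section 5.1, second main variable: "Differences in the quantification of the iron deposit assessed by nuclear magnetic resonance (NMR"), at weeks 0 and 56.
- Section 5.2: "Quantitative differences detected by the different cognitive tests (W0 and W56"), with MRI morphology, retinal measures and AD biomarkers on the same two-point scheme.

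The first of the two is a pre-treatment value. Section 4.1 describes the visits "with week 0 (w0) being the point of randomization and start of treatment". Sections 4.1.2 and 4.1.3 place the baseline neuropsychological tests at week −4 and the baseline MRI between weeks −4 and 0, which is also before treatment.

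**The concern.** With two measurements, one of them taken before any capsule, a repeated-measures model has a repeated factor only if the week-0 value is one of its responses. Such a model offers two tests that involve the arm:

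- The between-subjects group term compares the arm means averaged over weeks 0 and 56.
- The group-by-time term compares the changes.

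Section 5.4 separates within-group from between-group differences and mentions no interaction. An analyst who takes the sentence literally could therefore report the between-subjects test that SPSS prints. Randomised arms have the same expected week-0 mean, so that test averages the week-56 effect with a zero. What is at stake is the size of the estimate and the power for a main outcome, and the fact that one sentence allows tests that perform very differently.

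**Working it through.** **The plan's own figure.** None exists for this point. The minimum of 45 patients in Section 3.4 refers to the progression of cognitive deterioration, and no effect size or power is given for brain iron or any continuous outcome.

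**Inputs from the document.** Two-sided alpha 0.05 and 15% losses (Section 3.4); 60 recruited per arm (Section 8). Completers per arm: 60 × 0.85 = 51.

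**Assumptions.** Normal outcome with SD 1 at both visits; pre-post correlation r, which the document does not give, so a range is shown; no effect at week 0 and effect d at week 56.

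**Formulas.** With s = sqrt(2/51) = 0.198, the expected z is:

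- Group term, from (y0 + y56)/2: z = (d/2) / [sqrt((1+r)/2) × s]
- Group-by-time term, from y56 − y0: z = d / [sqrt(2(1−r)) × s]
- Week-56 ANCOVA on week 0: z = d / [sqrt(1−r²) × s]

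Power is Φ(z − 1.96). Set d so that ANCOVA has 80% power, that is z = 1.96 + 0.84 = 2.80. Substituting, the group term has z = 2.80 × sqrt((1−r)/2) and the group-by-time term z = 2.80 × sqrt((1+r)/2).

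Example, r = 0.5: group term z = 2.80 × 0.50 = 1.40, power Φ(−0.56) = 29%; group-by-time z = 2.80 × 0.866 = 2.43, power Φ(0.47) = 68%.

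| r | d (SD) | Group term | Group-by-time | ANCOVA |
|---|---|---|---|---|
| 0 | 0.555 | 51% | 51% | 80% |
| 0.3 | 0.529 | 38% | 62% | 80% |
| 0.5 | 0.480 | 29% | 68% | 80% |
| 0.7 | 0.396 | 19% | 73% | 80% |
| 0.8 | 0.333 | 14% | 76% | 80% |
| 0.9 | 0.242 | 9% | 78% | 80% |

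The group term needs 2/(1−r) times the ANCOVA sample: 4 times at r = 0.5 and 10 times at r = 0.8.

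**Fixed effect instead.** At d = 0.5 and r = 0.7: group term 0.25/(sqrt(0.85) × 0.198) = 1.37, power about 28%; group-by-time 0.5/(sqrt(0.60) × 0.198) = 3.26, about 90%; ANCOVA 0.5/(sqrt(0.51) × 0.198) = 3.54, about 94%.

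**Simulation check** (4,000 trials per value of r, r = 0.5 to 0.9). The mean group-term estimate was 0.49 to 0.51 of d, and the group-by-time estimate 0.99 to 1.01 of d.

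**Week 0 as covariate as well as response.** Given y0, the average (y0 + y56)/2 varies only through y56/2. Effect and standard error are both halved, so the p-value is that of the week-56 ANCOVA (simulated power 79.6% for both at r = 0.5, 78.1% for both at r = 0.7). The reported estimate is still half.

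**Ordering.** On the scale of d, the three variances are proportional to 2(1+r), 2(1−r) and 1−r². The third is never larger than either of the others, because 1−r and 1+r are at most 2.

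**The case against.** The strongest reply is that the averaged test is not in the text. Section 5.4 names no term. The outcomes are worded as differences at weeks 0 and 56, which suits a comparison of change at least as well as a comparison of averages. The contrast of ANOVA within arms with ANCOVA between arms implies some covariate, and the week-0 value is neither named nor excluded. Which term and which covariates apply is detail that an article may leave to the full protocol or to an analysis plan that is not shown here.

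Most of this stands, and it rules out several stronger conclusions that a reader might draw:

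- *That the plan fixes a test which halves the effect.* It permits that test and does not prescribe it.
- *That most of the power will be lost.* This follows only under the averaged reading without a week-0 covariate, and it depends on r. At r = 0 the figures are 51% against 80%.
- *That false positives are inflated.* All the tests reject about 5% overall when there is no effect. A chance week-0 difference enters the averaged contrast with weight (1+r)/2, not in full, and it raises rejection only in the subset of trials where such a difference occurs.
- *That every continuous outcome is affected.* Section 5.3 lists "Laboratory parameters (W0, W14, W28, W42, W56, and W62") and other variables with more than two visits, to which these figures do not apply. The dichotomous progression outcome falls under the categorical tests.

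The objection does not remove the point. The article states a method for a main outcome, and under each reading that method is either less precise than the week-56 ANCOVA or, with week 0 as both response and covariate, gives the same p-value with a halved between-subjects estimate.

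**Conclusion.** The point holds as an ambiguous and poorly chosen between-group method for the continuous outcomes measured only at weeks 0 and 56. Under one literal reading the estimate is half the treatment effect, and power is about 29% (r = 0.5) to 14% (r = 0.8) where week-56 ANCOVA has 80%. Under the group-by-time reading the test is valid and the effect is not halved; the cost is modest, with 68% to 78% power against 80% over r = 0.5 to 0.9.

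The halving follows from randomisation and the two-visit schedule alone. The power figures also assume 51 completers per arm, equal SDs, normality and an assumed r. The analysis plan, if there is one, may already name the term and the covariates.

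**What to change.** In Section 5.4, for continuous main and secondary variables measured at weeks 0 and 56, state that the between-group effect is the adjusted mean difference at week 56 with its 95% confidence interval. It comes from an ANCOVA with the week-56 value as outcome, arm as factor, and the week-0 value and the randomisation stratification factors of Section 3.4 as covariates. State also that the between-subjects main effect averaged over weeks 0 and 56 is not used.

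The cost is one sentence, written before unblinding. It needs no new visits, data or patients and runs in SPSS. There are two small downsides: patients without a week-0 value need simple baseline imputation, and the stratification factors use a few degrees of freedom.

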### Sample calculation and randomization

3.4

There are no data on the effects of phytate supplementation on mild cognitive impairment. The sample size has been calculated based on other dietary intervention studies on MCI considering an alpha risk of 0.05 and a statistical power of 0.8 (49). Bearing in mind that we anticipate that there will be a difference of 30% in the progression of cognitive deterioration between those assigned diet 1 and those assigned diet 2, for a bilateral hypothesis test, a power of 80%, an alpha of 0.05, and a percentage of losses of 15%, we would obtain a minimum sample of 45 T2DM patients. Randomization will be 1:1 using fixed size stratified blocks. The stratification factors will be APOE genotype, age (75 years), gender, duration of diabetes (10 years), and previous cardiovascular disease (50).

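### Section 5.4 names no method suited to the ordered MRI and retinopathy grades and leaves open whether ANCOVA or an unadjusted chi-square test applies; the chi-square route would cost substantial power.

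*Protocol article*

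**What the plan says.** Section 5.4 sets out two routes. The first covers the primary and secondary objectives: repeated-measures ANOVA within groups and repeated-measures ANCOVA between groups. The second is for categorical data: "Qualitative variables will be analyzed using the chi-square test" or McNemar's test. The next sentence promises that "The analysis will be adjusted for confounding variables". The significance rule is "A value of p<0.05 will be considered an indicator of a significant difference", and section 3.4 makes the testing two-sided ("for a bilateral hypothesis test").

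Section 5.2 lists three ordered outcomes, each assessed at weeks 0 and 56:
- "degree of atrophy of the medial temporal lobe (Scheltens score");
- white-matter lesions on the Fazekas scale;
- retinopathy stage on the Early Treatment Diabetic Retinopathy Study scheme.

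Section 5.4 mentions none of these by name. It does not say which variables are qualitative, and it offers no ordinal or rank method.

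**The concern.** A grade is neither a plain category nor a measurement, so it can be placed on either route of section 5.4, and the two routes do very different things.

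On the qualitative route:
- A Pearson chi-square across grades gives the same answer if the grades are shuffled, so it discards the order.
- Applied to the week-56 grade, it also discards the baseline grade, although section 5.2 frames these outcomes as differences or evolution between weeks 0 and 56.
- It takes no covariates. For any outcome on this route, the promise of adjustment in the following sentence cannot be kept.
- McNemar's test does use baseline, but it is a paired test on a two-level variable. It describes change within an arm and does not compare the arms.

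Brain morphology appears in the second main aim (section 2.1) and diabetic retinopathy in the first secondary aim (section 2.2). If the route stays open, a choice that strongly affects power could be made after the data are seen.

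**Working it through.** **Inputs from the article.** Two-sided alpha is 0.05 (sections 3.4 and 5.4). Recruitment is 60 per arm (section 8) and losses are 15% (section 3.4), so completers per arm = 60 × (1 − 0.15) = 51. The stated "a statistical power of 0.8" in section 3.4 belongs to cognitive progression. The article gives no power, effect, grade distribution or baseline correlation for the graded outcomes, so there is no figure of the plan to reproduce.

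**Assumptions (not in the article).** Baseline and week-56 values are bivariate normal with correlation ρ and are cut into ordered grades. The treatment shift is on the latent scale.

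**Check 1: fixed shift of 0.4 SD, 4 or 5 grades, 51 per arm.** Simulated power, with even and right-skewed grade distributions:

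| ρ | chi-square, week-56 grade | chi-square, worsened yes/no | rank ANCOVA with baseline grade |
|---|---|---|---|
| 0.5 | 27-32% | 28-38% | 53-56% |
| 0.7 | 27-31% | 40-52% | 64-69% |
| 0.85 | 27-31% | 59-72% | 81-87% |

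Type I error was about 5% for all methods. A separate run at the same sample size, shift and correlations gave 27-32%, 31-65% and 56-87% for the three columns overall. The yes/no test is the one most sensitive to where the grades are cut.

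Relative loss = 1 − (power of chi-square) / (power of rank ANCOVA). Bracketing the week-56 chi-square by the ends of the ranges:
- ρ = 0.7: from 1 − 31/64 = 52% to 1 − 27/69 = 61%.
- ρ = 0.85: from 1 − 31/81 = 62% to 1 − 27/87 = 69%.
- ρ = 0.5: the mid-points give 1 − 29.5/54.5 = 46%. Compared within each grade distribution in a repeat run, the loss stayed below half.

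**Check 2: shift tied to a fixed target.** The shift was set so that a baseline-adjusted analysis of the uncut values has about 85% power: shift = (1.960 + 1.036) × √(2(1 − ρ²)/51). At ρ = 0 this is 2.996 × 0.198 = 0.59; at ρ = 0.8 it is 0.59 × 0.6 = 0.36. Losses across 3 to 5 grades, computed from unrounded powers:

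| ρ | loss, chi-square on week-56 grade |
|---|---|
| 0 | 15-30% |
| 0.5 | 25-42% |
| 0.7 | 43-59% |
| 0.8 | 53-68% |
| 0.9 | 63-80% |
| 0.95 | 68-81% |

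For example, with 4 grades and ρ = 0.5, power is 48% against 71%, and 1 − 48/71 = 32%. With 5 grades and ρ = 0.7, it is 29% against 71%, and 1 − 29/71 = 59%. Chi-square on worsened yes/no lost 34-54%, above half only with 3 grades and ρ = 0.95. Ignoring order alone (chi-square against Wilcoxon on the week-56 grade) cost 14-48%.

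**Check 3: the other stated route.** With the grades entered as numbers in ANCOVA with baseline, power was within 3 points of rank ANCOVA in every setting of check 1. A group-by-time repeated-measures test had 41-83%.

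**The case against.** The strongest reply is that section 5.4 assigns the secondary objectives to ANCOVA first, and that section 5.2 speaks of a score and a scale. A reader could place the grades there, and on that reading almost nothing is lost. This stands. A reader might infer that the plan sends the grades to chi-square, but the text never classifies them.

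Other stronger readings also go too far:
- **More than half the power is lost.** This depends on a correlation that the article does not give and on testing the week-56 grade alone. A worsened yes/no comparison uses baseline, fits the week 0 to week 56 framing, and in the settings of check 1 loses less than half.
- **McNemar is the treatment test.** Section 5.4 separates within-group from between-group comparisons and nowhere gives McNemar that role.
- **All structural outcomes are affected.** The optical coherence tomography thicknesses and the vessel and perfusion densities are quantitative and fall under ANCOVA. The imaging main variable in section 5.1 is iron, not a grade.
- **The same fault reaches counts and concentrations.** Nothing in the article shows that "and number of lacunar infarcts detected" or "Inflammation mediators: TNF-a, IL-1b, and IL-6 (Multiplex") would be distributed in a way that defeats the stated methods.

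It can also be said that classifying variables is work for a statistical analysis plan, which is not shown. That limits the weight of the point but does not remove it: the article does fix a method for qualitative variables, and that method cannot deliver the adjustment promised beside it.

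**Conclusion.** The point holds in a limited form. Section 5.4 names no method made for ordered grades and does not say which of its two routes applies to the Scheltens, Fazekas and retinopathy grades. One route keeps nearly all the power. The other gives up part of it in every setting examined, with a week-56 loss at 51 per arm of roughly 15% to 81% depending mainly on baseline correlation. Slowly changing grades may well correlate highly over 56 weeks, which would favour the upper part of that range, but this is an assumption. The sizes also rest on the latent-normal model, the number of grades and the assumed shift. That chi-square ignores order and takes no covariates needs no assumption. The outcomes are secondary, so this is an inexpensive improvement and not a threat to the main result.

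**What to change.** In section 5.4, state that the week-56 Scheltens, Fazekas and retinopathy grades are compared between arms by a proportional-odds model, or by rank ANCOVA, with arm, baseline grade and the adjustment covariates. State that McNemar's test is used only to describe change within an arm. This settles the route before the data are seen and makes the promised adjustment possible. It costs a few sentences and a little analysis work, with no extra patients or visits. The one small downside is that the proportional-odds assumption has to be checked.

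### The sex-stratified analysis is justified by a prognostic difference and judged at p<0.05 with no estimate of whether the phytate effect differs between men and women

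*Protocol article*

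**What the plan says.** The Statistical analysis section (5.4) of the protocol article states that "women have a higher risk of dementia; therefore, an additional analysis will be carried out, stratifying results by sex". It then gives one criterion for all analyses: "A value of p<0.05 will be considered an indicator of a significant difference". Between-group differences are assigned to repeated-measures ANCOVA and qualitative variables to a chi-square or McNemar's test. Adjustment is promised for confounders that are not named. The article mentions no treatment-by-sex interaction and no other comparison of the effect between the sexes.

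Sex is also used at randomisation. Section 3.4 says "The stratification factors will be APOE genotype, age (75 years), gender", followed by diabetes duration and previous cardiovascular disease. The same section bases the sample size on the expectation that "there will be a difference of 30% in the progression of cognitive deterioration". The first main variable in section 5.1 is dichotomous progression. The Discussion plans 60 patients per arm.

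**The concern.** The premise and the method do not fit together. "women have a higher risk of dementia" describes who is more likely to deteriorate, whatever the treatment. The usual response is to include sex in the model. Whether phytate works differently in women and men is another question, and it is answered by estimating the difference between the two sex-specific effects. Splitting the results by sex and applying a 0.05 threshold in each half does neither job.

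The risk is one of interpretation. Each half of the sample has much less power than the whole, so the two p-values will frequently fall on opposite sides of 0.05 even when the effect is identical. A report showing significance in one sex and not in the other invites a conclusion of benefit in that sex only. Section 5.4 does not confine the sex analysis to one outcome, and section 5.2 lists many secondary variables, so the pattern could recur across the report.

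**Working it through.** **The plan's own figure.** Section 3.4 specifies "for a bilateral hypothesis test, a power of 80%, an alpha of 0.05, and a percentage of losses of 15"% and concludes that "we would obtain a minimum sample of 45 T2DM patients". No control rate is given, and the text does not say whether the 30% is absolute or relative, or whether 45 is per arm or in total. The figure therefore cannot be reproduced uniquely. It is reachable per arm: 50% vs 20% needs 39 per arm by the pooled two-proportion formula, which becomes 39/0.85 = 45.9, so 46, or 39 × 1.15 = 44.9, so 45. The 50% vs 20% scenario is an assumption; it does not appear in the article.

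**Patients per sex.** 60 per arm × 0.85 = 51 evaluable per arm. With an assumed even sex split, that is about 25 per arm per sex.

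**Power within one sex.** Power = Φ[(d − 1.96·SE0)/SE1], where SE0 = √(2p̄(1−p̄)/n), SE1 = √([p1(1−p1) + p2(1−p2)]/n), d = p1 − p2, p̄ is the mean of p1 and p2, and n is patients per arm. For 50% vs 20% and n = 25:
- SE0 = √(2 × 0.35 × 0.65/25) = 0.135
- SE1 = √((0.25 + 0.16)/25) = 0.128
- power = Φ[(0.30 − 0.264)/0.128] = Φ(0.28) = 0.61

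**Exactly one sex significant, same true effect in both.** With equal strata this is 2 × power × (1 − power). For 50% vs 20% it is 2 × 0.61 × 0.39 = 0.48. Over the assumed control rates, at 25 per arm per sex:

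| Reading of the 30% | Control vs phytate | Power per sex | Exactly one sex p<0.05 |
|---|---|---|---|
| Absolute | 35% vs 5% | 0.77 | 35% |
| Absolute | 40% vs 10% | 0.70 | 42% |
| Absolute | 50% vs 20% | 0.61 | 48% |
| Absolute | 60% vs 30% | 0.57 | 49% |
| Absolute | 65% vs 35% | 0.57 | 49% |
| Relative | 30% vs 21% | 0.11 | 19% |
| Relative | 40% vs 28% | 0.14 | 24% |
| Relative | 50% vs 35% | 0.18 | 30% |
| Relative | 60% vs 42% | 0.24 | 37% |

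The sex split matters little. With 60/40 (31 and 20 per arm) and 50% vs 20%, the powers are 0.71 and 0.51, and exactly one sex is significant with probability 0.71 × 0.49 + 0.51 × 0.29 = 0.49 to 0.50.

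**At the planned 80% power, without a control rate.** The overall standardised effect is 1.96 + 0.84 = 2.80. In each half it is 2.80/√2 = 1.98. Power per sex is Φ(1.98 − 1.96) = 0.51, and exactly one sex is significant in 2 × 0.51 × 0.49 = 50% of trials. Both are significant in 26% and neither in 24%.

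**No effect in either sex.** At least one within-sex test is significant with probability 1 − 0.95² = 9.75%.

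**What an interaction test does instead.** When the effect is identical in both sexes it rejects at a nominal 5% (5.6–7.2% in simulation with a simple Wald test at these cell sizes). Its power against a real difference is low. Take 50% vs 20% in one sex and 50% in both arms of the other, with 25 per arm per sex: SE = √((0.25 + 0.16 + 0.25 + 0.25)/25) = 0.191, so power = Φ(0.30/0.191 − 1.96) = Φ(−0.39) = 0.35.

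**The case against.** The strongest reply is that this is one clause in a condensed article. An interaction term is the sort of detail left to the full protocol or analysis plan, which are not shown and may contain it. That point stands as far as absence goes, and nothing here says that the full plan lacks such a test. What remains is what the article does state: a rationale, a method and a threshold. The rationale does not lead to the method, and the method cannot support a comparison between the sexes.

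A reader might infer that the investigators intend to compare within-sex p-values, or to claim benefit in one sex. The article does not say so. Neither the aims nor the hypothesis includes a sex difference, and the wording can be read as plain reporting of results by sex, which is reasonable. The misreading is a risk that the text leaves open, not a stated plan.

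A reader might also take a figure near one half as the expected rate. The documents do not support a single figure, because control rate, sex split and the meaning of 30% are all unstated; the relative reading gives much lower values.

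Finally, randomisation stratified by sex helps balance the arms within each sex. That is true and useful, but it does not test whether the effect differs.

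**Conclusion.** The point holds as a limited one. Section 5.4 justifies a sex-stratified analysis by a prognostic difference and judges it at p<0.05. Separate within-sex tests cannot show that the phytate effect differs by sex. With an identical true effect, exactly one sex would be significant in about 35–49% of trials on the absolute reading, about 20–37% on the relative reading, and about 50% if overall power is the planned 80% with an even split. The first two ranges assume about 25 evaluable patients per arm per sex, with control rates of 35–65% and 30–60% respectively.

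It would go too far to infer that the main result is compromised. The analysis is described as additional, and the main between-group comparison does not depend on it.

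**What to change.** In section 5.4, or in the analysis plan if that is where the detail belongs:
- Keep the results by sex, but as descriptive effect estimates with 95% confidence intervals.
- Add a treatment-by-sex interaction estimate with 95% confidence interval and p-value. For continuous outcomes this is a term in the ANCOVA already planned. For dichotomous progression, a chi-square test has no term to extend, so use logistic regression with the interaction, or a test of homogeneity across the sex strata such as Breslow-Day.
- Adjust the main analysis for sex, as a randomisation factor. This deals with the prognostic reason the article gives.
- State that no sex-specific claim will be made from within-sex p-values.

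The cost is small: a little more analysis and a few sentences, with no new data, since sex is already recorded and used at randomisation. The downside is the interaction test's low power (about 35% even for 30 points in one sex and none in the other, under the assumptions above). The text should therefore also say that a non-significant interaction is not proof of equal effects.
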